### Statistical analysis

Analysis will follow a Statistical and Health Economics Analysis Plan which will have been approved a priori by the Trial Steering Committee. Data presentation and analysis will be in accordance with Consolidated Standards of Reporting Trials (CONSORT) guidelines. Baseline characteristics will be reported by trial arm using percentages, means (SDs) or medians (interquartile ranges) as appropriate. The repeated measures of primary and secondary outcomes will be plotted by trial arm.

The main analysis will consist of a linear mixed regression (with random intercept for patient to control for the repeated follow-ups) with an interaction between the intervention effect and the assessment time adjusted for pre-operative function and recruitment centre. The use of these interactions terms will allow us to assess and single out the specific effect of the intervention on LEFS at 12 months post-operative, and then identify the intervention-specific effects at 3 and 6 months post-operative (secondary outcomes). The regression will then be adjusted for imbalanced individual characteristics between arms at baseline. Other types of generalised linear mixed models will be considered if the former approach is not fitting the distribution of the residuals of the regressed (transformed) primary or secondary outcomes. The model will finally be adjusted for type of additional physiotherapy treatment received (physiotherapy received that is not delivered as part of the intervention). The trial is not powered for such adjustments and it will only inform us on their potential impact on the intervention effect.

The analyses will be conducted on an intention-to-treat basis with and without imputation of missing primary outcome data. A multiple imputation (MI) by chained equations under a missing at random framework stratified by randomization arm will be used [47]. These imputed results will be contrasted with other imputation strategies as discussed by White and colleagues [48]. The same modelling strategy will be used to investigate the intervention effect on the KOOS, HADS and patient satisfaction. A sensitivity analysis will investigate the intervention effect using a per-protocol analysis. Information clustering at the recruitment centre level will be addressed using a fixed-effect indicator and clustering of outcomes by surgeon will be investigated and modelled if required. We will also compare the mean/median primary outcome by physiotherapist for patients receiving the intervention and any significant differences will be used to conduct exploratory sub-group analyses. Given the differences in outcomes after TKR for men and women [49], exploratory analysis will be undertaken to investigate the impact of gender.

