### Assessment times

Participants will be followed up for 12 months after TKR. Participants will be asked to complete questionnaires before their surgery and at 3 months, 6 months and 12 months after their surgery. Post-operative questionnaires will be posted to participants, followed by a postal reminder and a telephone call to non-responders.

In addition to the questionnaires, further information will be collected by telephone. At 2 weeks post-operative, all participants will be telephoned and asked to complete the five-level EuroQol questionnaire (EQ-5D-5 L) [37]. Patients who attend the intervention will be telephoned 1 month after completion of the classes to complete a short telephone survey to evaluate the classes and home exercise programme. All participants who complete the 12-month follow-up of the trial will be contacted by telephone and asked if they would be willing to complete a telephone survey about the experience of trial participation. A flow chart of trial participation is provided in Fig. 1.

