### Sample size

The minimal clinically important difference (MCID) for the LEFS is 9 scale points [26]. In our feasibility study, we observed a pooled standard deviation (SD) of 18.4 and a rate of missing LEFS score of 9 % in the intervention group and 35 % in the usual-care group at 6 months post-operative. For the purposes of the sample size calculation we assumed a similar SD for the LEFS at 12 months post-operative, due to the lack of relevant published data. To account for the uncertainty induced by estimating parameters from a small feasibility study, we adjusted the assessed sample by an inflation factor of 1.12^2^, a value derived from the 80 % upper confidence limit of the SD estimate [46]. We also accounted for a missing data rate of 35 %, although we are implementing additional measures to improve LEFS completion rates (e.g. completion of the primary outcome measure over the telephone with non-responders). Therefore, a sample of 256 patients will allow us to detect a MCID (9 points) in the LEFS between trial arms at 12 months post-operative, assuming a power of 80 %, a two-sided 5 % significance level and accounting for up to 35 % missing data and an ‘inflation factor’ of 1.12^2^.

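### The random-intercept model takes the 12-month standard error from variance averaged over 3, 6 and 12 months, so the primary interval and p-value are off if LEFS variance changes during recovery

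*Protocol article*

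**What the plan says.** All references are to the protocol article.

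- **Model (Statistical analysis).** The main analysis is a "linear mixed regression (with random intercept for patient to control for the repeated follow-ups"). Its fixed part has arm, time and their interaction, with pre-operative function and centre as covariates. No random slope, visit-specific residual variance, unstructured covariance or robust standard error is named.
- **Target (Statistical analysis).** The interaction is there to "single out the specific effect of the intervention on LEFS at 12 months post-operative"; the 3- and 6-month effects are secondary.
- **Visits (Assessment times).** Questionnaires are due before surgery and "at 3 months, 6 months and 12 months after their surgery".
- **Response to misfit (Statistical analysis).** "Other types of generalised linear mixed models will be considered if the former approach is not fitting the distribution of the residuals". The trigger is the shape of the residuals, not variance by visit or correlation between visits.
- **Variance (Sample size).** The only SD is 18.4, pooled, at 6 months in the feasibility study. For the primary time point, "we assumed a similar SD for the LEFS at 12 months post-operative, due to the lack of relevant published data".
- **Missing data (Sample size; Statistical analysis).** In the feasibility study 9% of LEFS scores were missing in the intervention arm and 35% "in the usual-care group at 6 months post-operative". The trial's analyses are to be run with and without chained-equations multiple imputation under missing at random, stratified by arm.

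**The concern.** A patient random intercept with independent, equal-variance residuals imposes one variance at all three visits and one correlation for every pair of visits. The only primary quantity is the 12-month contrast, yet its standard error then borrows variance from 3 and 6 months. The Background says function plateaus at around 12 months, so the two earlier visits fall during recovery, when the spread of scores may well differ from the final spread. Nothing in the protocol shows that it is constant.

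At stake are the width of the primary confidence interval and the true size of the nominal 5% test. The same modelling strategy is planned for KOOS, HADS and satisfaction, so the restriction carries over to them. A smaller, conditional issue is bias: a likelihood analysis of incomplete data under missing at random relies on a correct covariance model.

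**Working it through.** **1. The plan's own figure.** Inputs from Sample size: difference 9 ("The minimal clinically important difference (MCID) for the LEFS is 9 scale points"), SD 18.4, two-sided 5%, power 80%, inflation 1.12², 35% missing.

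- Per arm: 2 × (1.960 + 0.842)² × 18.4² / 9² = 65.6, rounded up to 66.
- 66 × 1.2544 = 82.8, rounded up to 83.
- 83 / 0.65 = 127.7, rounded up to 128 per arm, 256 in total.

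The 256 is reproduced. It uses one time point, so the covariance choice does not alter it.

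**2. Standard error with complete data.** With free arm-by-time means and no missing data, the estimated 12-month contrast is the difference in 12-month means. Its true variance is 2 × SD12² / n per arm. The random-intercept model instead uses 2 × mean(SD3², SD6², SD12²) / n. Hence

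model SE / true SE = √mean(SD²) / SD12, and type I error = 2 × [1 − Φ(1.96 × ratio)].

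The SDs by visit are assumptions; the protocol gives only 18.4 at 6 months.

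| Assumed SDs 3/6/12 | mean SD² | Model SE | True SE | Ratio | Type I error |
|---|---|---|---|---|---|
| 14/16/19 | 271.0 | 2.06 | 2.38 | 0.87 | 8.9% |
| 16/18.4/20 | 331.5 | 2.28 | 2.50 | 0.91 | 7.4% |
| 18.4 throughout | 338.6 | 2.30 | 2.30 | 1.00 | 5.0% |
| 19/17/15 | 291.7 | 2.13 | 1.88 | 1.14 | 2.6% |

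Unequal correlations alone do not disturb this: in simulation with equal SDs and decaying correlations the complete-data SE ratio was 0.99.

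**3. After the planned multiple imputation.** Two separate simulations (1,500 and 2,000 trials per scenario, 128 per arm) used 12-month missingness of 35% v 9% depending on the 6-month score, imputed by arm, then took the 12-month contrast with the random-intercept SE.

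| Assumed SDs | Bias (points) | Type I error in the two runs |
|---|---|---|
| 14/16/19 | under 0.1 | 7.4%, 7.7% |
| 16/18.4/20 | under 0.1 | 5.6%, 6.2% |
| 19/17/15 | under 0.1 | 2.5%, 2.6% |
| 18.4 throughout | under 0.1 | nominal; 5.3% in the second run |

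Imputation removes the bias. The SE error shrinks but remains.

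**4. Without imputation.** With 35% v 9% missing at 12 months, a true effect of 9, and 400,000 simulated patients per arm:

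- missing completely at random: no bias, even with rates differing by arm;
- compound symmetry true: no bias;
- otherwise, with missingness depending on the 3- or 6-month score: bias between −1.04 and +1.07 points, at most 1.07/9 = 12% of the target difference, in either direction;
- unstructured covariance: bias within about 0.1 point throughout.

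In trials of planned size with SDs 14/16/19, correlations 0.75/0.55/0.75 and missingness depending on the 6-month score, the non-imputed random-intercept analysis had type I error 11.2%, against 5.0% to 5.6% for unstructured covariance across the unequal-SD scenarios. In a further set of scenarios (800 trials each, Monte Carlo error about 0.8 points) the unstructured model ranged from 4.3% to 7.7%, mostly 4% to 6%.

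**5. Baseline coefficient.** No baseline-by-time term is named. Suppose raw SDs are equal but the correlation with baseline falls 0.6/0.5/0.4 (assumed). A common coefficient corresponds to 0.5, and the residual variances are 0.65, 0.75 and 0.85 of the raw variance. The ratio is √(0.75/0.85) = 0.94 and the type I error 6.6%. This is a small effect, but it means that equal raw SDs alone do not guarantee equal residual variances.

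**The case against.** **No evidence that variances differ.** The protocol assumes the 12-month SD is similar to the 6-month one, and if the SDs are similar the model is near nominal. This stands: the table shows what could happen, not what is known. But similarity was adopted for lack of data, for the sample size, and says nothing about 3 months.

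**Detail belongs to the analysis plan.** The article defers to a Statistical and Health Economics Analysis Plan that is not shown. A random intercept does not strictly exclude visit-specific residual variances, and that plan may specify them. This is fair, and the point rests on the ordinary reading of the model as stated. The article does, however, name the within-patient structure, and its only stated reason to change model is residual distribution.

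**Dropout is already handled.** A reader might infer that the unequal 9% and 35% missingness will bias the primary effect. The protocol does not support that. It plans arm-stratified multiple imputation, which removed the bias in simulation. The rates are 6-month missing scores from a 46-patient feasibility study, not 12-month dropout in this trial, and telephone completion for non-responders has been added. Bias also needs missingness that depends on earlier scores. What is left concerns the non-imputed analysis, which is still one of the two planned results; the protocol does not say which of them is primary for the clinical outcome.

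**The 11.2% figure.** It is tempting as a headline, but it combines rising SDs, score-dependent missingness and no imputation, all chosen as inputs. It should not be quoted as the expected error of this trial.

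**Conclusion.** The point holds as a weakness in a stated method, and it should be corrected. On the ordinary reading, the primary standard error depends on equal variance at three visits, an assumption the protocol neither supports nor needs. Over assumed SDs from 14/16/19 to 19/17/15, type I error runs from about 9% to 2.6% with complete data and from about 7.5% to 2.5% after the planned imputation; it is near nominal if SDs are equal. The error is anti-conservative if the spread grows towards 12 months and conservative if it shrinks.

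Bias is secondary: at most about 1 LEFS point in the scenarios tried, in the non-imputed analysis only, and only if missingness both depends on earlier scores and differs by arm.

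The algebra of the averaged variance is certain. The sizes rest on assumed SDs, correlations and missingness, because the protocol gives no SD at 3 or 12 months and no correlations between visits.

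**What to change.** In the analysis plan, before any unblinded analysis:

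- replace the patient random intercept by an unstructured 3x3 within-patient covariance for 3, 6 and 12 months, fitted by REML with Kenward-Roger degrees of freedom;
- include time, arm-by-time and baseline-LEFS-by-time terms and centre, and take the 12-month contrast from this model;
- state in advance a fallback that keeps time-specific variances if the model does not converge, such as heterogeneous Toeplitz with robust standard errors;
- use the same model for the imputed and the non-imputed analyses.

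The cost is six covariance parameters instead of two and a small convergence risk. No new data are needed and the sample size stays 256. With equal SDs and equal correlations, little is lost: in simulation the two models gave the same 12-month standard error to within 0.01 point (for example 2.30 v 2.29 with complete data). The simulations tested the unstructured covariance with normal critical values, not the Kenward-Roger adjustment.

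### The main mixed model names only a plain adjustment for pre-operative function, so a slope pooled over 3, 6 and 12 months adjusts the 12-month LEFS contrast and can bias the non-imputed result in either direction

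*Protocol article*

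**What the plan says.** The Statistical analysis section of the protocol article sets out a linear mixed regression with a patient random intercept, "with an interaction between the intervention effect and the assessment time adjusted for pre-operative function and recruitment centre". The stated purpose of the interaction is to "single out the specific effect of the intervention on LEFS at 12 months post-operative"; the 3- and 6-month effects are secondary. Participants "complete questionnaires before their surgery and at 3 months, 6 months and 12 months after their surgery", so three post-operative visits enter the model.

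On missing data, the Sample size section reports from the feasibility study "a rate of missing LEFS score of 9 % in the intervention group and 35 % in the usual-care group at 6 months post-operative". It allows for 35% missing and lists steps to do better, including "completion of the primary outcome measure over the telephone with non-responders". The Abstract and the Statistical analysis section both plan the intention-to-treat analysis with and without imputation. The imputation is by chained equations under missing at random, separately by arm. The clinical text does not say which of the two results leads, whereas the Health economic analysis section names the imputed data as the basis of its primary results. The same modelling strategy is extended to KOOS, HADS and satisfaction.

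**The concern.** One interaction is named, intervention by assessment time. Pre-operative function is listed as an adjustment with no time interaction, so on the plain reading a single slope is estimated from all three visits and applied at 12 months. Pre-operative function need not predict the 3-month and 12-month scores equally well.

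With complete data this hardly matters, because randomisation (stratified on pre-operative LEFS) keeps the arms alike at baseline. With missing data, the patients observed at 12 months may differ between arms in pre-operative function. A slope that is wrong for 12 months then corrects that difference by the wrong amount, and the remainder goes into the treatment contrast. The contrast affected is the primary one.

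**Working it through.** **The plan's own figure.** With a 9-point difference, SD 18.4 × 1.12 = 20.608, 80% power and two-sided 5%: n per arm = 2 × (1.960 + 0.842)² × 20.608² / 9² ≈ 82.3, rounded up to 83. Allowing for 35% missing: 83 / 0.65 = 127.7, so 128 per arm and 256 in total. This matches the article.

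**Standard error at 12 months.** If the feasibility rates of 9% and 35% recurred: 18.4 × √(1/(128 × 0.91) + 1/(128 × 0.65)) = 2.64 points.

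**Mechanism.** Approximately,

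bias ≈ (12-month slope − pooled slope) × (mean pre-operative LEFS of observed intervention patients − that of observed usual-care patients).

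If either factor is zero, there is no bias.

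**Assumed inputs, not in the article.** Pre-operative LEFS SD 16; residual correlation between visits 0.6; slopes by visit as shown; missingness related to pre-operative LEFS with log-odds k per SD; and the 9%/35% split recurring in the trial.

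**Worked case.** Slopes 0.6/0.5/0.4, k = 1, lower-function patients more often missing. The observed arms then differ by −3.4 points at baseline. With a pooled slope near 0.5, bias ≈ (0.4 − 0.5) × (−3.4) = +0.34. Fitting the model to a very large simulated sample (400,000 patients, true effect zero) gives:

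| Slopes at 3/6/12 months | Who is missing (k = 1) | One slope: bias | Slope by visit: bias |
|---|---|---|---|
| 0.6/0.5/0.4 | lower function | +0.35 to +0.48 | about 0 |
| 0.7/0.5/0.3 | lower function | about +0.7 to +0.95 | about 0 |
| 0.4/0.5/0.6 | lower function | −0.34 to −0.48 | about 0 |
| 0.5/0.5/0.5 | lower function | within 0.02 of 0 | within 0.02 of 0 |
| 0.7/0.5/0.3 | unrelated to function | within 0.03 of 0 | within 0.04 of 0 |

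The lower end of each range in the first three rows applies when the same patients are missing at every visit; the upper end applies when they are missing at 12 months only.

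**Milder and harsher cases.** In simulated trials of 128 per arm, slopes 0.5/0.45/0.4 gave 0.12 points (k = 0.4) and 0.23 (k = 0.8). Slopes 0.7/0.5/0.2 gave 0.60 and 1.11. A stress case (0.8/0.5/0.2, k = 3) reached about 2.3 points.

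**Size in context.** 0.35/9 = 4% and 0.95/9 = 11% of the minimal important difference; 0.35/2.64 = 0.13 and 0.95/2.64 = 0.36 standard errors. At N = 256 the approximate type I error in these moderate cases is 5.2% to 6.8%.

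**Imputation.** Chained equations by arm, with pre-operative LEFS and the other visits as predictors, followed by the same one-slope model, left a bias of −0.03 to +0.01. Imputation puts every randomised patient back into the 12-month comparison, so the second factor in the formula returns to about zero.

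**Precision.** At N = 256 the SD of the 12-month estimate, one slope against slope by visit, was 2.59 v 2.59 in a milder case and 2.54 v 2.49 in a steeper one. The extra terms cost nothing material.

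**The case against.** The strongest reply is that the article summarises a model whose full form belongs in a separate analysis plan, which is not shown. It does not say that a baseline-by-time term is excluded, nor whether pre-operative function enters as the continuous score or as the high/low stratum. That is fair, and it limits the point to the model as published. The model is nevertheless written out with one named interaction, and an analysis plan that followed the wording would carry the weakness over.

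The second reply is that arm-stratified imputation is already planned. This largely stands: it can remove the bias. But the article does not list the imputation variables, and it keeps the analysis without imputation as a planned primary analysis.

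A reader might infer that the error favours the intervention. The documents do not support this. That direction needs lower-function patients to be missing and the slope to fall with time (or both conditions reversed), and the article reports neither. Changing just one of the two reverses the sign.

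A reader might also take the 9% and 35% figures as proof of bias. They come from a 46-patient feasibility study at 6 months, which the trial plans to improve on. Unequal rates alone do no harm: with equal slopes, or missingness unrelated to pre-operative function, the two models agree to within 0.01 points even at those rates.

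**Conclusion.** The point holds as a minor one. As written, the main model adjusts the 12-month LEFS contrast with a slope pooled over three visits. The non-imputed contrast can therefore be biased in either direction, by roughly 0.1 to 1 LEFS point under mild to moderately strong assumptions, against a standard error of about 2.6. About 2 points is reached only in extreme cases.

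These sizes rest entirely on assumed slopes, missingness strength, baseline SD and residual correlation, and on the feasibility missingness rates recurring. Two conditions must both hold: a slope that changes over time, and missingness that shifts the pre-operative mix differently in the two arms. The article establishes neither. It is a case for a better model specification at almost no cost and does not show that the trial's result will be wrong.

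**What to change.** Add a pre-operative LEFS by assessment time term to the main model, next to the planned intervention by assessment time term, so that the 12-month contrast is adjusted with the 12-month slope. Where the same strategy is used for outcomes with a baseline measure (KOOS, HADS), add the matching baseline by time term. State this in the analysis plan before outcome data by arm are seen.

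The cost is about two extra parameters per model (three slopes in place of one), no new data, no change to N = 256 and no material precision. Centre by time is not needed for this point: nothing in the calculation involves centre.

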### Randomisation

Participants will be randomised with a 1:1 treatment allocation to the intervention group or usual care group 2 weeks after TKR. Prior to randomisation, eligibility criteria will be reassessed through contact with participants and review of operation notes. Randomisation with allocation concealment will be conducted by means of a computer-generated code, administered centrally and communicated via the Internet (through the Bristol Clinical Trials and Evaluation Unit). Randomisation will be stratified by pre-operative function measured by the Lower Extremity Functional Scale [27] (categorised as high or low function based on mean scores from a published study with a similar patient cohort [28]) and recruitment centre (Southmead Hospital or Emersons Green Treatment Centre). Blinding of participants and trial personnel to treatment allocation will not be possible due to the nature of the intervention.

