### Usual care

At both recruitment centres, usual physiotherapy after discharge following TKR surgery comprises information and advice on knee-specific and functional exercise. Referral for outpatient physiotherapy is on a needs-only basis when deemed appropriate by a member of the clinical care team. Prior to hospital discharge, patients are assessed on an individual basis by the inpatient physiotherapy team at each centre, and patients with poor range of motion or muscular weakness are referred for outpatient community-based physiotherapy. This referral is at the discretion of the hospital’s physiotherapy or orthopaedic team. General practitioners (GPs) and consultants can also refer patients for outpatient physiotherapy as appropriate. Use of physiotherapy services by participants in both trial arms will be recorded in the trial questionnaires.

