## Discussion

This project is a fully powered RCT to evaluate the long-term clinical effectiveness and cost-effectiveness of a novel group-based outpatient physiotherapy intervention following TKR in addition to usual care. The trial includes patients with all levels of functional aspirations, and emphasises the concept of participation in valued activities as a basis for effective and appropriate rehabilitation goals. Our approach aims to both improve function for those patients who may otherwise have unfavourable outcomes, and assist patients who are recovering well to achieve more demanding goals.

A strength of this trial is that the design of the intervention and trial were informed by prior feasibility work [25]. In particular, the feasibility work highlighted the importance of complementing the collection of outcome measures by postal questionnaire with telephone calls to maximise completion rates. This has previously been shown to be an effective strategy with a similar patient population [56], although with the increasing uptake of technology, online questionnaires may be a useful alternative data collection method for future trials. Another strength of this trial is the 12-month follow-up period, which will allow assessment of the long-term impact of physiotherapy on patient outcomes and resource use. However, in addition to patient-reported outcome measures, the trial may have benefitted from the inclusion of more objective measures of function, such as muscle strength or gait analysis, as these capture different dimensions of function [57]. Another limitation of the trial which warrants acknowledgement is the lack of blinding, because of the group-based nature of the physiotherapy intervention. Blinding in trials of physiotherapy is often challenging and only a quarter of physiotherapy trials are blinded [58]. There is a risk that lack of blinding will introduce bias as outcome data will be self-reported by participants who will know which treatment they have been allocated to. A recent meta-epidemiology study found that lack of blinding in physiotherapy trials can lead to an underestimation of the treatment effects compared to trials with blinding, although this was not statistically significant [58]. In addition, while the trial is powered for our primary analysis, other analyses are purely exploratory in nature and will be interpreted as such.

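### The last LEFS model adjusts for non-trial physiotherapy received, largely a post-randomisation variable tied to poor recovery, so the change it produces cannot be read as the impact of extra physiotherapy

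*Protocol article*

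**What the plan says.** Under Statistical analysis, the main model for LEFS is a linear mixed regression with "an interaction between the intervention effect and the assessment time adjusted for pre-operative function and recruitment centre". A further fit adjusts for characteristics imbalanced at baseline. The sequence then ends: "The model will finally be adjusted for type of additional physiotherapy treatment received", meaning physiotherapy outside the trial classes. The article adds: "The trial is not powered for such adjustments and it will only inform us on their potential impact on the intervention effect". The Discussion says of everything beyond the primary analysis that "other analyses are purely exploratory in nature and will be interpreted as such". The same modelling strategy is to be used for KOOS, HADS and satisfaction, so the step appears to carry over to them.

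Three other places bear on what this covariate is:

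- **Randomisation:** "Participants will be randomised with a 1:1 treatment allocation to the intervention group or usual care group 2 weeks after TKR". The same section says that participants and trial personnel cannot be blinded.
- **Usual care, first referral route:** the inpatient physiotherapists judge each person individually before they leave hospital. The rule they apply is that "patients with poor range of motion or muscular weakness are referred for outpatient community-based physiotherapy".
- **Usual care, second referral route:** "General practitioners (GPs) and consultants can also refer patients for outpatient physiotherapy as appropriate". No time limit is given.

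Use of physiotherapy in both arms is recorded in the trial questionnaires. Under Assessment times, the post-operative ones are at 3, 6 and 12 months.

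**The concern.** The covariate is treatment received, not a baseline characteristic. Three features make it unsuitable for ordinary regression adjustment.

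1. Much of it happens after randomisation.
2. It is given to people who are doing badly, and doing badly also lowers later LEFS.
3. Allocation can plausibly change it. Someone attending weekly classes may recover faster and need no referral, or a clinician who knows about the classes may see no reason to refer.

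A variable that treatment can affect, and that shares unmeasured causes with the outcome, is both a mediator and a collider. Conditioning on it can create or remove an apparent treatment effect even when extra physiotherapy does nothing. The article's caveat is about power. This problem is bias, which a larger sample would not reduce.

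What is at stake is interpretation. Needs-based physiotherapy is available in both arms, so if the trial result is null or small, readers will look to this model for an explanation. An effect that shrinks on adjustment would invite the conclusion that extra physiotherapy accounts for it, and the model cannot support that.

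**Working it through.** **The plan's own figure.** Inputs from Sample size: difference 9, SD 18.4, inflation 1.12² = 1.2544, two-sided 5%, power 80%, 35% missing.

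- Per arm: 2 × (18.4 × (1.960 + 0.842) / 9)² = 65.6.
- Inflated: 65.6 × 1.2544 = 82.3, rounded up to 83.
- Allowing for missing data: 83 / 0.65 = 127.7, rounded up to 128, so 256 in total.

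This matches the article. The extra-physiotherapy covariate plays no part in it.

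**Illustration A: with baseline adjustment.** The article gives no uptake figures, so everything except the SD of 18.4 and the 9-point effect is assumed. There are 500,000 simulated patients per scenario, a single time point and a yes/no covariate.

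- Early recovery: R = 18.4 × (0.5·B + √0.75 × 0.8·U) + d·A, where A is arm, B is baseline function, U is unmeasured recovery and d is the class effect.
- Extra physiotherapy: logit P(M = 1) = −1 − s·R/18.4 + g·A.
- LEFS: Y = R + e·M + 18.4 × √0.75 × 0.6 × noise.

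Y is regressed on A and B, without and then with M. The standard error of the arm coefficient is about 2 × 15.9 / √500,000 = 0.05. Shifts were taken before rounding.

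| s (link to poor recovery) | g (direct arm effect on uptake) | d | e | Uptake, usual care / intervention | Without M | With M | Shift |
|---|---|---|---|---|---|---|---|
| 1.5 | 0 | 0 | 0 | 32% / 32% | −0.02 | −0.01 | 0.01 |
| 0 | −0.7 | 0 | 0 | 27% / 15% | 0.04 | 0.04 | 0.00 |
| 0.5 | −0.7 | 0 | 0 | 28% / 16% | −0.09 | −0.57 | −0.48 |
| 1.5 | −0.7 | 0 | 0 | 32% / 21% | 0.00 | −1.17 | −1.17 |
| 1.5 | 0 | 9 | 0 | 32% / 21% | 9.06 | 7.81 | −1.25 |
| 1.5 | −0.7 | 9 | 0 | 32% / 13% | 8.99 | 6.86 | −2.14 |
| 0 | −0.7 | 0 | 4 | 27% / 15% | −0.50 | −0.03 | 0.46 |
| 0.5 | −0.7 | 0 | 4 | 28% / 16% | −0.50 | −0.53 | −0.03 |
| 1.5 | −0.7 | 0 | 4 | 32% / 21% | −0.37 | −1.14 | −0.76 |

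- Rows 1 and 2: with no effect of either treatment there is no shift if uptake is unrelated to arm, or if it is unrelated to recovery.
- Rows 3 to 6: extra physiotherapy does nothing (e = 0), yet adjustment moves the arm effect. In row 5 arm acts on uptake only through recovery, and that is enough.
- Rows 7 to 9: the classes have no direct effect and extra physiotherapy is worth 4 points, so correct adjustment should give 0. It does when uptake is unrelated to recovery (row 7). When uptake follows poor recovery, the estimate hardly moves (row 8) or moves away from 0 (row 9).

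Row 8 is the clearest. The whole arm difference runs through extra physiotherapy, 4 × (0.16 − 0.28) = −0.48, but comparing the two models suggests that none of it does.

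**Illustration B: larger uptake gaps, no baseline covariate.** True effects are all 0, the correlation of recovery with LEFS is 0.4 to 0.6, and the logistic slope is about 1 to 2 (odds ratio e¹ = 2.7 to e² = 7.4 per SD of recovery).

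| Uptake, usual care / intervention | Shift, LEFS points |
|---|---|
| 30% / 30% | 0.0 |
| 30% / 25% | −0.2 to −0.8 |
| 40% / 20% | about −1.2 to −2.8 |
| 50% / 15% | about −2.2 to −4.8 |

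With no true effects, swapping the arms' uptake reverses the sign, so the direction is not known in advance either.

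**The case against.** **No conclusion rests on this model.** The main analysis omits the covariate and is by intention to treat. The step comes last, is offered only as information, and falls under the Discussion's exploratory label. This stands, and it limits the point to interpretation. It does not remove the point: the caveats cover precision and status, while the stated purpose of showing the impact on the intervention effect is what the model cannot deliver.

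**Bias is possible, not certain.** The article does not say that uptake differs by arm, and the classes are given on top of the same usual care. With uptake unrelated to arm the shift is about 0. This stands. A reader might infer that the adjusted effect is necessarily biased, but the documents support only that it is liable to be.

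**Part of the referral precedes randomisation.** The sentence on poor range of motion or weakness concerns assessment before discharge. If discharge falls within 2 weeks, which is an assumption, allocation cannot affect that decision. This stands for the referral decision. It does not rescue the planned covariate, which is treatment received and also includes later GP and consultant referrals.

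**The larger shifts need extreme inputs.** The −4.8 figure combines a 35-point uptake gap, a slope of 2, a correlation of 0.6 and no baseline LEFS in the model. This stands. Setting it against the 9-point MCID might suggest a threat to the trial's result, which the documents do not support.

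**The analysis plan may say more.** It is not shown. The adjustment itself is nevertheless fixed in the article.

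**Conclusion.** The concern holds in limited form. As described, the final adjustment is liable to bias and cannot show the impact of extra physiotherapy on the intervention effect. This rests on three conditions: part of the physiotherapy is received after randomisation, uptake follows poor recovery, and uptake depends on arm directly or through recovery. The article's own account supports the first two. The third is plausible in an unblinded trial but not documented.

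Size and direction are unknown. Under the assumptions above, the shift is about 0 with equal uptake and no effect of arm on recovery before referral. It reaches about −2 points in the baseline-adjusted illustration, and nearly −5 only in an extreme corner of the unadjusted one. The primary intention-to-treat estimate, its interpretation as the effect of adding classes to usual care, and the sample size of 256 are untouched.

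**What to change.** - Remove this model as an adjusted estimate of the intervention effect, for LEFS and for the secondary outcomes that share the strategy.
- Report type and amount of extra physiotherapy by arm descriptively, as part of the care received under each policy.
- If its influence is to be estimated, name the quantity wanted (for example a direct effect, or the effect had no extra physiotherapy been given), use a causal mediation or estimand-based method that handles confounding by recovery, state its assumptions and label it exploratory.
- Use referral made before discharge as a baseline covariate only if it is recorded as preceding randomisation.

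The first two changes cost a few sentences in the analysis section and analysis plan. Physiotherapy use is already collected in both arms, and sample size and trial conduct do not change. The optional causal analysis adds work. The optional baseline covariate needs a dated referral record, which the article does not say is collected.
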